### Determination of colonisation

Colonisation will be defined by the microbiology result of nasal washes taken at 2-, 7- and 14-days post inoculation. Nasal washes will be plated on to culture media and incubated overnight at 37°C in 5% carbon dioxide (CO
_2_). Colonies will be confirmed as
*S. pneumoniae* using classical microbiological techniques including (i) typical draughtsman-like colony morphology, (ii) the presence of α-haemolysis, (iii) optochin sensitivity and (iv) Gram-positive diplococci. Typing by latex agglutination will be done using a commercial kit to confirm pneumococcal serogroup. Isolates will be frozen at -80
^o^C for storage. Results from the cultured nasal wash will also be confirmed using polymerase chain reaction (PCR) based methods of bacterial detection.

Monitoring of colonisation – monitoring of colonisation will be performed by microbiology analysis of nasal washes.

### Safety during colonisation

A three-day course of amoxicillin and a digital thermometer will be given on the day of inoculation. These will be carried by the participants for immediate treatment after phone consultation should the participant develop any symptoms as described on the participant safety advice leaflet
^14^. Participants will be required to make text message/phone contact with a specified member of the research team before 1200 hrs every day for 7 days post-inoculation
*regardless of whether they have symptoms or not*. Should they not make contact by the specified time, a member of the research team will contact the participant. If no contact is made, then a prior defined ‘secondary contact’ will be telephoned. During the post-inoculation period, participants will have access to a 24/7 on-call telephone service until the end of the study.

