### Study endpoints

Primary endpoint: detection of the inoculated pneumococci by classical culture methods, at any time point, from nasal wash recovered from the participants at days 2, 7 and 14 following pneumococcal challenge.

Secondary endpoints: confirmation of robust clinical and laboratory methods for sample capture and processing. Acceptability of study and methods.

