### Exclusion criteria

Previous pneumococcal vaccinationHIV-infection: HIV testing will be performed by trained personnel certified in HIV Testing Services (HTS). “Determine” or “Unigold” will be used as the first line tests. Any participants identified as HIV-infection positive will be referred to the governmental system for infection confirmation, treatment and follow up.Close physical contact (e.g. sleeping in the same room or nursing) with at risk individuals (children under 5 years age, immunosuppressed adults, elderly, chronic ill health)Allergy to penicillin/amoxicillinAcute illness○ Current illness○ Acute illness within 3 days prior to inoculation○ Antibiotic treatment within 2 weeks of inoculation

Chronic illness that may impair immune response or impair ability to comply with study procedures and safety monitoring (e.g. HIV, diabetes).Taking immunosuppressive medication that may include but are not limited to steroids and steroid nasal spray.Pregnancy - minimise risk of pneumococcal diseaseInvolved in another clinical trial unless observational or in follow-up (non-interventional) phaseHistory of drug or alcohol abuse. This is very difficult to ascertain in a history therefore we will exclude people reporting drinking alcohol more than twice per week.History of Smoking○ Current regular smoker (smokes daily/smokes > 5 cigarettes per week) - minimise risk of pneumococcal disease○ Recent smoker i.e. within the last 6 months - minimise risk of pneumococcal disease○ Ex-smoker with a significant smoking history (>10 pack years) – minimise risk of pneumococcal diseaseUnable to give informed consentIn case of any uncertainty or concern, the PI will take clinical responsibility for the decision.

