***Inoculation***

• Inoculation - using a P200 micropipette, 0.1ml saline containing the desired dose (see
Figure 2) of pneumococcus will be instilled into the nose. The participant will be seated in a semi-recumbent position. After inoculation, the participant will remain in this position for up to 15 mins. They will be given a post-inoculation advice sheet (including emergency contact details), thermometer, a course of amoxicillin (500mg TDS for 3 days) and a daily symptom log to complete.

• Dose escalation and sham inoculation - We have adopted a step-wise approach to escalating the inoculation dose. The protocol is designed to: a) minimise the possibility that we try repeatedly to attain carriage at a dose in which it is unlikely to occur; b) maximise safety by inoculating small groups (in case adverse events occur) before continuing on to larger groups in which we will be able to give reasonable precision to estimate carriage rates. Groups 1, 2 and 3 will receive increasing doses of pneumococcal inoculation as explained in
Figure 2. Briefly, 20,000 cfu/naris (Group 1) is not expected to achieve carriage. If 80,000 cfu/naris achieves more than 4 from 9 participants with carriage, then the study will end at that point. Sham inoculation with 0.9% normal saline has been incorporated into the study design to assess whether any potential observed effects in participants are pneumococcal challenge-related or simply reflect the study conditions. Participants will receive only one inoculation dose. If carriage is not achieved after inoculation, participation will be concluded upon completion of visit eight.

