### Termination of carriage

All study participants who are nasally colonised with pneumococcus at the end of the study will be asked to take oral amoxicillin 500mg three times daily for 3 days. This will be communicated at visit 7, or by telephone in the unlikely event of only visit 7 samples (day 14) showing carriage.

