Figure 2 since an alternative participant will be recruited in the case of withdrawal of a participant. Participants missing study visits so that no day 2, 7 or 14 data is available will be withdrawn from the study and their data excluded from data analysis. A new participant will be recruited in such a case and this new participant will be allocated to the same pneumococcus / sham inoculation as the participant ID for the withdrawn participant was randomised to. The primary feasibility endpoint will be assessed, at each of the five analysis time points using colonisation results data from all participants that are required for that stage’s analysis and that have completed visit 7 (d14). Other analyses are primarily descriptive or make use of censored data techniques, so that no advanced missing data methods will be used in these analyses. Data collection forms are provided in extended data
^21^. 

***Statistical significance and multiple testing.*** Success (feasibility) of the study will be decided according to the decision rules stated on
Figure 2.

Success (safety) of the study will decided by decision of the DSMB & TC upon revision of each SAE and SUSAR. For this reason, no formal null hypothesis significance testing will be performed for the main analysis and no multiple testing adjustment will need to be made.

For secondary analyses, statistical significance is defined as p<0.05, but effect sizes / parameter estimates, exact p-values and confidence intervals will be stated. While we will report on statistical significance, results will be presented and discussed in accordance with recent guidance
^22^.

***Technical details.*** All analyses and figures will be performed using the R environment (v.3.5.3 or later) for statistical computing and graphics and associated packages
^23^.

***Feasibility.*** The primary analysis aims to establish feasibility of the Malawi CHIM: does one of the three doses (20,00, 80,000, 160,000 CFU) lead to ≥50% nasal colonisation?

To assess this, the decision algorithm specified in the study design (

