Moderate illness events are defined as fever with temperature >37.5°C, shivering, headache, new rash, drowsiness, cough, new earache and or new eye infection. Participants will be clearly instructed to call the research team at any time of the day upon development of these symptoms. During the telephone assessment participants will be screened for severe symptoms and requested to attend either the research clinic (office hours) or Mwaiwathu hospital (outside of office hours) for medical assessment. If severe symptoms are identified on telephone assessment, participants will be asked to take antibiotics from their supplied emergency pack and attend Mwaiwathu hospital. Study doctors will assess the participants at either the research clinic or Mwaiwathu and offer appropriate treatments. The assessment will be fully documented within study records including rationale for any treatments.

*Severe illness*

Severe illness events are defined as any symptoms that cause serious concern to participants following inoculation. We have purposefully taken a conservative approach to encourage participants to seek early medical advice and treatment if they are concerned. Participants will be counselled as to what symptoms the study team may be particularly concerned about during the consent process
^24^. These would include any potential symptoms of sepsis. In the event of severe illness, participants are requested to start taking the provided emergency antibiotics, directly attend Mwaiwathu hospital and contact the study team. A study doctor will attend the patient in Mwaiwathu and offer appropriate treatments. The assessment will be fully documented within study records including rationale for any treatments.

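### A challenged participant who takes the emergency amoxicillin before any positive wash, stays in follow-up and has only negative washes counts as a non-carrier, which lowers the observed carriage rate and pushes the decision towards escalation

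*Protocol article*

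**What the plan says.** All references are to the protocol article.

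- **Endpoint (Study endpoints).** The primary endpoint is "detection of the inoculated pneumococci by classical culture methods, at any time point, from nasal wash" on days 2, 7 and 14. One positive wash makes a carrier.
- **Decision rule (Figure 2 legend).** A dose needs at least 2 carriers among the first 6 challenged, then at least 4 among all 9. Otherwise the next dose is tried.
- **Emergency pack (Inoculation; Safety during colonisation).** Everyone leaves the inoculation visit with amoxicillin 500 mg three times daily for 3 days. Of the pack and thermometer the protocol says "These will be carried by the participants for immediate treatment after phone consultation", should leaflet symptoms develop.
- **Ending carriage (Termination of carriage).** Participants still colonised at the end "will be asked to take oral amoxicillin 500mg three times daily for 3 days". Drug, dose and duration match the pack.
- **Entry (Exclusion criteria).** One criterion is "Antibiotic treatment within 2 weeks of inoculation".
- **Who is counted (Statistical analysis, Missing data).** Each decision uses the culture results of all participants needed for that stage who completed visit 7. Replacement follows withdrawal. In addition, "Participants missing study visits so that no day 2, 7 or 14 data is available will be withdrawn from the study", and they are left out of the analysis and replaced under the same allocation. Taking the pack is not among these triggers.

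**The concern.** The 2/6 and 4/9 thresholds ask whether a dose produces carriage. A wash taken after a course that the protocol itself uses to clear carriage cannot answer that for someone who had not yet tested positive. The entry criterion on antibiotics shows that the authors regard such treatment near inoculation as a problem, but the counting rule makes no matching provision after inoculation.

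The error runs one way. A true carrier can be scored as a non-carrier, and treatment does not turn a non-carrier into a carrier. The observed rate is therefore biased downwards and the decision is pushed towards a higher dose. At 160,000 CFU per naris, where no further step exists, it is pushed towards concluding that the model does not work. With 6 or 9 per decision, and with the algorithm itself as the primary analysis, one such case can settle the outcome. Unneeded escalation exposes new volunteers, which the abstract says the design is meant to limit.

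**Working it through.** **Inputs.** Thresholds ≥2/6 and ≥4/9 come from the Figure 2 legend. (The Inoculation section words the 80,000 threshold as more than 4 of 9; the legend's version is used here.) The true carriage rate p is 0.5 or 0.6, from the 50-60% the legend expects at 80,000 CFU. The article states no power. Its figures that can be checked do reproduce: (8+4) + (8+4) + 12 = 36 participants, of whom 27 are challenged and 9 sham, and 2 + 2 + 1 = 5 assessments.

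**No one treated early.** With X1 ~ Bin(6, p) and X2 ~ Bin(3, p):

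P(pass) = P(X1=2)·P(X2≥2) + P(X1=3)·P(X2≥1) + P(X1≥4)

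- p = 0.5: (15/64)(4/8) + (20/64)(7/8) + 22/64 = 376/512 = 0.734
- p = 0.6: 0.138×0.648 + 0.276×0.936 + 0.544 = 0.893

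**One of the first six treated early and negative throughout.** That person contributes a certain zero, so X1 ~ Bin(5, p):

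- p = 0.5: (10/32)(4/8) + (10/32)(7/8) + 6/32 = 158/256 = 0.617
- p = 0.6: 0.230×0.648 + 0.346×0.936 + 0.337 = 0.810

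**Variants, by the same formula:**

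| Early-treated, scored negative | p = 0.5 | p = 0.6 |
|---|---|---|
| None, or replaced | 73.4% | 89.3% |
| One of the first six | 61.7% | 81.0% |
| One of the last three | 63.7% | 82.6% |
| Two of the first six | 46.9% | 67.7% |

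One case costs 10 to 12 percentage points at p = 0.5 and 7 to 8 at p = 0.6.

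**Without fixing the number treated.** Let f be the share of true carriers masked in this way. The effective rate is p(1−f). The article gives no value for f, so the range is an assumption.

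| f | p = 0.5 | p = 0.6 |
|---|---|---|
| 0 | 73.4% | 89.3% |
| 1% | 72.4% | 88.6% |
| 2% | 71.4% | 87.8% |
| 5% | 68.2% | 85.4% |
| 10% | 62.6% | 80.8% |
| 20% | 50.5% | 69.3% |

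**How often the pack might be used.** Two sections differ. Safety during colonisation links use to leaflet symptoms after a telephone consultation. Under moderate illness, Safety considerations and assessment says "participants will be asked to take antibiotics from their supplied emergency pack" when the call identifies severe symptoms; the severe illness paragraph likewise has participants start it. The choice of trigger affects f, and the text does not settle it.

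**The case against.** **The scoring is inferred.** No sentence says that a treated participant is a non-carrier. The rule sits under Missing data, and a separate SAP that is not shown could add a provision. Withdrawal for any reason also leads to replacement, so someone ill enough to be treated might leave and be replaced. This part stands: the point covers only those who stay in follow-up. For them the article does state which results enter each decision and when replacement occurs, and the count follows from that.

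**The event may be rare.** The article reports over 1000 Liverpool participants with no active infection and no related serious adverse effects. A positive day 2 wash before treatment still counts, so for early carriers the window is about two days. With 1 or 2% of carriers masked, the loss at p = 0.5 is only 1 to 2 points. This stands too. The larger figures are conditional on a case occurring.

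**A remedy can overcorrect.** Dropping everyone treated before a positive wash, whenever that happened, removes negatives selectively. If 10% of non-carriers were dropped (assumed), a true 40% rate would read 0.40/(0.40 + 0.60×0.90) = 42.6%, and the pass chance would rise from 50.5% to 56.8%. Replacing only challenged participants could also reveal allocation to the blinded clinical team. Both objections are right, and the fix is narrowed accordingly.

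**Stronger readings.** A reader might infer that anyone who takes the pack is scored as a failure; a positive wash before or after treatment still makes a carrier. A reader might infer that too low a dose would be chosen; the push is upwards. A reader might infer that treated participants are disproportionately carriers; the documents do not show this, and sham inoculation is there partly to learn whether effects are challenge-related.

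**Conclusion.** The concern holds in a limited form. Three conditions must coincide: the pack is taken before any positive wash, the participant stays in follow-up, and every wash is negative. The stated rules then put that person in the denominator as a non-carrier without replacement. The observed rate is biased downwards, which favours escalation or, at the last dose, a finding of infeasibility.

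If one of the first six challenged at a dose is affected, the chance of passing falls from 73% to 62% at true 50% carriage and from 89% to 81% at 60%. These figures assume independent outcomes, the Figure 2 thresholds and a treated participant who remains culture-negative. The two-stage form applies to 20,000 and 80,000 CFU, since the 160,000 group is a single cohort of 9 challenged.

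The documents do not support saying that a wrong escalation is likely, because they give no frequency of early pack use and it is probably low. The case for acting is that the correction is cheap and the decision is the trial's primary analysis.

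**What to change.** This changes analysis handling only. In the Missing data text of Statistical analysis:

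1. State that a participant is not evaluable for the dose decision if an antibiotic active against the strain is started before the day 7 wash, no earlier wash was positive and all later washes are negative.
2. Replace such a participant through the existing same-allocation mechanism, applying the rule to challenged and sham participants alike so that blinding is kept.
3. Keep as carriers all participants with any positive wash. Keep as non-carriers those negative at days 2 and 7 before treatment; the Figure 1 legend already calls carriage seen only at day 14 unlikely.
4. Record the start date of any antibiotic, and keep all treated participants in the safety data.
5. Report the carriage rate and the decision with the non-evaluable participants also coded as carriers and as non-carriers.

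Separately, reconcile the triggers for using the pack in Safety during colonisation and in Safety considerations and assessment.

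The cost is an occasional replacement participant, with a wait for that person's day 14 result, and possibly a slightly higher observed rate, which item 5 makes visible. The text should also say how such a replacement counts towards the maximum of 36.

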We will schedule inoculations such that participant monitoring (to day 20) is completed at each pneumococcal dose (20,000 and 80,000) prior to escalation. The feasibility study research investigators [name], [name], [name] and [name] have successfully worked together to safely deliver pneumococcal CHIM studies in Liverpool and will transfer this knowledge and experience to MLW. No episodes of pneumococcal infection or serious unexpected serious adverse reactions (SUSARS) have occurred in any of our participants whether they had no carriage, natural carriage or experimental carriage. We will transfer and rigorously implement the Standardised Operating Procedures to ensure safety for Malawian participants.

***Participant safety procedures.*** We will provide all participants with a safety information sheet
^14^. This sheet classifies symptoms into mild, moderate and severe. We will take a proactive approach for participants, with daily contact throughout the study and enquiry about development of any symptoms. We will also encourage participants to report development of any symptoms with 24-hour medical cover throughout the study visit schedule. In the event of illness, we will apply standardised operating safety procedures for participants. The research team will pay for any costs associated with these procedures and participants will incur no out of pocket expenses.

*Mild illness*

Mild illness is defined as development of any new symptom that is of concern to the participant during the study period. These may include mild coryzal symptoms such as blocked or runny nose. Participants will be encouraged to contact the research team by telephone within office hours. During the telephone assessment participants will be screened for potentially concerning moderate and severe symptoms. If there is any concern, participants will be invited to the research clinic for a detailed clinical assessment by one of the study doctors. The assessment will be fully documented within study records including rationale for any treatments and/or required modifications to study procedures.

*Moderate Illness*

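### The general rule for the emergency amoxicillin sets a phone consultation first and makes no exception for severe illness that the participant recognises, where the graded procedure does not require one

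*Protocol article*

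**What the plan says.** Two parts of the protocol article tell participants when to use the emergency pack.

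The general rule is under Safety during colonisation. The amoxicillin and a thermometer are handed out on the day of inoculation and carried "for immediate treatment after phone consultation should the participant develop any symptoms as described on the participant safety advice leaflet". The same paragraph adds that "participants will have access to a 24/7 on-call telephone service until the end of the study".

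The graded rules are under Safety considerations and assessment, in the subsection Participant safety procedures. Of the safety information sheet, cited there by the same reference as the leaflet in the general rule, it says: "This sheet classifies symptoms into mild, moderate and severe". The three grades then read as follows.

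- Mild illness: "Participants will be encouraged to contact the research team by telephone within office hours".
- Moderate illness: "Participants will be clearly instructed to call the research team at any time of the day upon development of these symptoms". The call screens for severe symptoms. If it finds any, the participant is told to take the pack and go to hospital.
- Severe illness: "participants are requested to start taking the provided emergency antibiotics, directly attend Mwaiwathu hospital and contact the study team". Of the symptoms of particular concern to the team, this paragraph says: "These would include any potential symptoms of sepsis". It explains its broad definition thus: "We have purposefully taken a conservative approach to encourage participants to seek early medical advice and treatment if they are concerned".

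**The concern.** The general rule places a consultation between symptom and treatment for everything on the leaflet. The severe-illness paragraph puts the antibiotics first in its list and contact with the team last. A reader who follows the general rule literally would have a participant with possible sepsis telephone before taking the first dose. A reader who follows the severe-illness paragraph would not.

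What is at stake is participant safety in a study that infects healthy volunteers on purpose. The severe-illness paragraph says its definition was kept broad so that help and treatment come early, and a compulsory call beforehand works against that aim. The general rule also stands under the heading where staff would naturally look for how the pack is to be used. Both instructions are stated in the article, so this is a disagreement between two rules and not a detail left to a fuller document.

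**Working it through.** No arithmetic formula applies and the plan gives no figure to reproduce. The check is a comparison of texts.

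**Step 1: scope of the general rule.** It applies to any symptom on the leaflet. The leaflet grades symptoms into three levels, one of which is severe. Severe symptoms are therefore inside the rule.

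**Step 2: is there an exception elsewhere?** The Inoculation section says the pack is handed out and gives no rule on when to take it. The list under Study design to ensure safety describes the tablets as being for an emergency and is silent on a call. Participant safety procedures does not say that it overrides the general rule, and the general rule does not refer to it. Nothing reconciles the two.

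**Step 3: first action on each route.**

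| Route | First action stated | Agrees with a consultation before treatment? |
|---|---|---|
| Mild illness | Telephone the team | Yes |
| Moderate illness | Telephone the team | Yes |
| Severe symptoms found on a telephone assessment | Call has taken place; pack then taken on instruction | Yes |
| Severe illness recognised by the participant | Start the pack, go directly to hospital, contact the team | No: a prior call is not a condition |

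Three of the four routes agree and one differs. This is a count of routes and does not measure risk.

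**Step 4: is the fourth row read correctly?** The severe-illness sentence joins its three actions with commas and a final conjunction, so it fixes no strict order between antibiotics and contact. But contact comes last, hospital is to be attended directly, and the moderate-illness paragraph just before it states the call-first order in plain terms. Where the authors wanted a call first, they wrote it. The natural reading is that severe illness was meant to be handled differently.

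**Step 5: how far the fourth route matters within its grade.** Severe illness is defined by what seriously concerns the participant. Self-recognition is therefore how that paragraph expects the grade to be entered, so the difference does not lie in a remote corner of it.

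**The case against.** The best reply is that the general rule is a short overview and the graded procedures are the operative text, so a sensible reader lets the specific rule govern. The general rule stresses immediacy, does not forbid earlier use, and comes with a line staffed at all hours. Participants are also offered three nights of accommodation after challenge, with twice-daily checks as a possible substitute. They act on the leaflet, the post-inoculation advice sheet and the counselling at consent, not on a sentence in a journal article. The leaflet may already give the right order.

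Most of this stands, and it keeps the point small. It does not make the two instructions agree. No sentence gives one precedence over the other, and a telephone line reduces the delay without removing the condition.

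Three stronger readings are tempting, and the documents do not support them.

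- A reader might infer that the protocol bars the pack until a call has been made, or that it expressly tells severely ill participants not to call. Neither section says so. The general rule contains no word of exclusion, and the severe-illness paragraph does ask for contact.
- A reader might infer that all severe illness is in conflict. Severe symptoms identified during a call are treated after a consultation, as the general rule says.
- A reader might infer that the general rule sends every mild symptom to antibiotics, conflicting with the milder grades and clearing carriage before the nasal washes. Treatment after a consultation leaves the decision to that consultation, which is what the mild and moderate procedures describe. The document shows no effect on the carriage endpoint.

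**Conclusion.** The point holds in a limited form and is minor. For severe illness that the participant recognises, the general rule sets a prior consultation and the severe-illness paragraph does not. On the other three routes they agree.

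The conclusion rests on two readings: that the safety leaflet and the safety information sheet are the same document, which the shared reference supports, and that listing contact last means a call is not a precondition. The document gives neither a frequency of severe illness nor a time to reach the on-call line, so no delay can be calculated. Whether any participant would be misdirected depends on the leaflet, which is not shown. The finding therefore concerns the protocol text alone. No sample size, decision rule or endpoint is affected.

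**What to change.** Add an exception to the sentence on amoxicillin under Safety during colonisation: *except in severe illness, where the participant starts the pack at once, attends hospital directly and contacts the team, as set out under Participant safety procedures.* Leave the mild and moderate procedures as they are.

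Then confirm that the safety leaflet and the post-inoculation advice sheet give the same order.

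The cost is one clause and a check of the participant materials, with whatever approval the Amendments section requires. It needs no extra participants, visits, procedures or analyses. Study status reports eight participants already inoculated at the 20,000 CFU dose, so the clarification is best made promptly for those still to come.
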